**9 Economic evaluation**

Women are afflicted by urinary tract infections (UTIs) at a rate that is much higher than that for men. Although UTIs are often regarded as common or innocuous, they are associated with a considerable expense to society and nuisance for patients. This economic evaluation will be undertaken to answer the relevant decision, within two separate clinical studies, to select the most economically efficient non-antibiotic treatment versus antibiotic prophylaxis (‘care as usual’) compared in pre- en post-menopausal women with recurrent UTIs. These prospective, comparative cost studies are set up alongside the randomized clinical trials RCT-A and RCT-B.

Costs are defined from the societal perspective, regarding direct medical and non-medical and indirect non-medical costs associated with inpatient and acute outpatient management of UTI. Total resource costs are related to clinical cure, the risk of recurrent infection and evolving bacterial resistance issues and therefore reflect the economic efficiency of cranberry capsules or capsules with two strains of lactobacilli (non-antibiotic prophylaxis) compared to antibiotic prophylaxis (‘care as usual’), at the medium-term (12 months after study inclusion).

The economic evaluation will be designed as a cost-effectiveness analysis (CEA). Thereby, primary analyses will offset incremental costs (measured in Euro) against gains in the primary endpoints (number of recurrence of symptomatic UTI and time until the first occurrence of antibiotic resistance in urine or faeces) secondary analyses against quality of life years (QALYs) gained. Cost effectiveness will be calculated cost per prevented UTI. The time horizon of this cost-analysis will be limited to the study-period. The costs of treatment will be discounted against 4%. Cost reduction and better outcomes may go hand in hand, as complications associated with UTIs or treatment failures will generate additional hospital stay, patient re-evaluation, return visits, patient dissatisfaction and pharmacological reservicing costs associated with a new course of therapy.

Unit costs, if available, of used resources will be determined based on current Dutch guidelines (22). Data on resources used for in/out-patient treatment are collected from the hospital information system (with continuous registration) and financial reports. The lack of available information of medical and non-medical resource use in the patient setting and productivity loss implies more comprehensive data collection. Therefore, complementary volumes will be retrieved by self-reported questionnaires during the study period. Protocol driven costs will be excluded from the calculations.

The economic analysis will be expanded with a sensitivity-analysis to extrapolate the consequences of implementation and actual performance of using non-antibiotic treatment in (non-)complicated UTIs. In a sensitivity analysis different scenarios will be evaluated in relation to the generalisability of the results. A simulation model will be developed, based on the statistical results for subsequent analyses (1) evaluating the sensitivity for primary and secondary endpoints as well as cost parameters and (2) extrapolating to the Dutch target population and (depending on medium-term outcomes) to long-term scenarios.

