**2 Study objectives and endpoints**

**2.1 Study objectives**

**2.1.1 Primary objectives**

- To determine if non-antibiotic prophylaxis is a non-inferior treatment in the prevention of recurrent symptomatic UTIs compared to the currently standard antibiotic prophylaxis in pre- and post-menopausal women (non-inferiority trial)
- To assess if non-antibiotic prophylaxis reduces the selection of antibiotic resistant micro-organisms in urine and faeces compared to currently standard antibiotic prophylaxis in pre- and postmenopausal women
  - 1. **Secondary objectives**
- To evaluate if non-antibiotic prophylaxis compared to antibiotic prophylaxis in pre- and post-menopausal women lead to differences in the:

- incidence of asymptomatic bacteriuria

- incidence of other (non-urinary tract) infections

- incidence of adverse events

- quality of life

- To evaluate the costs and cost-effectiveness of non-antibiotic prophylaxis compared to antibiotic prophylaxis in the prevention of recurrent UTIs in pre- and post-menopausal women.

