**2.2.2 Secondary endpoints**

- incidence of asymptomatic bacteriuria

- incidence of other infections

- adverse events

- quality of life

- costs per prevented UTI

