**8 Statistical analysis**

**8.1 Power and sample size calculations**

### Non-inferiority part: It is known from clinical practice that many women are afraid of contracting resistant bacteria. For that reason they do not want to take antibiotic prophylaxis over an extended period of time. These women are even willing to take non-antimicrobial prophylaxis with a lower success rate in preventing UTIs compared to antimicrobial prophylaxis. Therefore, we accept a 10 percent lower success rate of the non-antibiotic compared to the antibiotic prophylaxis.

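### Cost per prevented UTI suits this non-inferiority design badly: on the planning rates its denominator is negative, and if non-inferiority is shown the effect interval will usually include zero

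*Protocol*

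**What the plan says.** Section 2.2.2 of the protocol lists one economic endpoint, "costs per prevented UTI". Section 9 repeats it: "Cost effectiveness will be calculated cost per prevented UTI". The same section sets the direction of the comparison, namely "to select the most economically efficient non-antibiotic treatment versus antibiotic prophylaxis", and its form: "primary analyses will offset incremental costs (measured in Euro) against gains in the primary endpoints". Those endpoints are the number of symptomatic recurrences and the time to first resistance. It also plans "secondary analyses against quality of life years (QALYs) gained", followed by sensitivity analyses and a simulation model. It voices the hope that "Cost reduction and better outcomes may go hand in hand".

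The clinical design points the other way for UTIs. The first primary objective (section 2.1.1) is "To determine if non-antibiotic prophylaxis is a non-inferior treatment in the prevention of recurrent symptomatic UTIs". Section 8.1 states that "we accept a 10 percent lower success rate of the non-antibiotic compared to the antibiotic prophylaxis", and plans on 95% success with TMP-SMX against 85% with cranberries and 87% with lactobacilli. Nothing says what is reported if the effect difference is zero or negative.

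**The concern.** A cost per event prevented is easy to read when the new treatment is expected to prevent more events at extra cost. Here the new treatment is compared with an active control that is expected to prevent more. Two difficulties follow.

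- **Sign.** With a negative denominator, a positive ratio means money saved while more UTIs occur. The same positive ratio could mean money spent to prevent UTIs. A negative ratio can mean either dominated or dominant.
- **Precision.** If the difference in UTIs is compatible with zero, the ratio can be arbitrarily large in either direction, and its confidence set is not an ordinary bounded interval.

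At stake is the secondary objective on cost-effectiveness. A reader given only the named ratio could not tell which decision it supports.

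**Working it through.** **Inputs from section 8.1:** success 95% (TMP-SMX), 85% (RCT-A) and 87% (RCT-B); accepted deficit 10 percent, taken here as percentage points; one-sided alpha 0.05; power 0.80; 130 analysable women per arm.

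**Step 1, the plan's own figure.** For 95% v 85%:

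n = [1.645 × √(2 × 0.90 × 0.10) + 0.842 × √(0.95 × 0.05 + 0.85 × 0.15)]² / 0.10² = 110.2, so 111.

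With the continuity correction, (110.2/4) × [1 + √(1 + 4/(110.2 × 0.10))]² = 129.5, so 130. The stated 130 is reproduced, which confirms that the sizing takes a 10-point deficit as its planning difference.

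**Step 2, the denominator on the planning rates.** Effect = p(non-antibiotic) - p(antibiotic), with SE = √[p₁(1 - p₁)/130 + p₂(1 - p₂)/130].

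| Trial | Effect | SE | 95% interval | Women per 130 | Chance of a positive observed effect |
|---|---|---|---|---|---|
| RCT-A | 0.85 - 0.95 = -0.10 | 0.037 | -0.172 to -0.028 | 13 more with a UTI | 0.3% |
| RCT-B | 0.87 - 0.95 = -0.08 | 0.035 | -0.149 to -0.011 | about 10 more with a UTI | 1.1% |

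**Step 3, the sign.** The protocol gives no cost difference. I assume 20 euro, and 100 euro to show a range, with an effect of 0.10 in either direction. Increments are non-antibiotic minus antibiotic.

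| Non-antibiotic arm is | Ratio at 20 euro | Ratio at 100 euro |
|---|---|---|
| cheaper, less effective | -20/-0.10 = 200 | 1000 |
| dearer, more effective | 20/0.10 = 200 | 1000 |
| dearer, less effective | 20/-0.10 = -200 | -1000 |
| cheaper, more effective | -20/0.10 = -200 | -1000 |

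The first two rows call for opposite readings but share one figure, and so do the last two. The size is also fragile: 20/0.01 = 2000 against 20/0.10 = 200.

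**Step 4, the ratio if non-inferiority is shown.** Non-inferiority holds when effect - 1.645 × SE exceeds -0.10. Take 95% control success and an observed effect of -0.046 (90.4% in the non-antibiotic arm). Then SE = √(0.95 × 0.05/130 + 0.904 × 0.096/130) = 0.032 and the lower limit is -0.046 - 0.053 = -0.099, which just passes. The two-sided 95% interval is -0.046 ± 0.063, that is -0.109 to +0.017. At assumed control rates of 90% and 85% the corresponding intervals are -0.112 to +0.044 and -0.114 to +0.066. All span zero. A non-inferior result therefore comes with an effect interval that includes zero, unless the non-antibiotic arm is clearly better.

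**Step 5, the alternative summary.** Let ΔC and ΔU be the differences in cost and in UTIs per woman (non-antibiotic minus antibiotic), and λ the value of one UTI avoided. Net monetary benefit is -λ × ΔU - ΔC. Treating 0.10 as a UTI difference for illustration, cheaper with more UTIs gives 20 - 0.10λ and dearer with fewer gives 0.10λ - 20. These have opposite signs at every λ except 200, so the two cases that share one ratio are separated. There is no division, so the interval stays bounded.

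**The case against.** The strongest reply is that the quoted sentence does not say which arm does the preventing. The ratio can be read as the antibiotic's cost per UTI it prevents, or as savings per extra UTI accepted. Labelled in that way it is interpretable, so a negative difference does not make it invalid. That stands. However, section 9 frames the comparison as non-antibiotic against care as usual and speaks of gains, and it does not supply the label.

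A reader might infer that the analysis cannot tell the quadrants apart at all. The documents do not support that. Section 9 requires incremental costs and incremental effects, so both signs will be known; the ambiguity arises when the ratio is reported alone.

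A reader might also infer that a near-zero denominator is what the protocol expects. It is not: at -0.10 and -0.08 both intervals exclude zero. Near zero is the situation if the trial succeeds, not the planning case.

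Nor does the whole economic evaluation fail. Time to resistance is a primary economic measure on which the planning rates (30% v 15% resistance) favour the non-antibiotic arm, and QALYs, sensitivity analyses and a model are also planned.

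Finally, net benefit and quadrant rules are often left to an analysis plan, which is not shown here. That is fair for the method details. The named endpoint, though, is a choice the protocol itself makes.

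**Conclusion.** The point holds in a limited form. The protocol fixes, as its one listed economic endpoint, a ratio whose expected denominator is negative on its own planning rates (-0.10 and -0.08). When non-inferiority is shown without clear superiority, the effect interval will usually include zero.

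The sizes rest on the planning proportions of women with success, whereas the ratio needs the difference in mean number of UTIs, which the protocol does not give. The rates are not like for like either: the Rationale presents 95% as a reduction in episodes, and 87% as the share without UTI among women recolonised with lactobacilli after estriol. The direction is clear; the magnitudes are illustrative, and the euro figures are assumptions. This is a cheap improvement to a secondary endpoint and does not touch the primary analysis.

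**What to change.** In sections 2.2.2 and 9, define the economic outcome as incremental cost and incremental number of symptomatic UTIs per woman, non-antibiotic minus antibiotic, each with its interval. Summarise the two by incremental net monetary benefit over a stated range of values per UTI avoided, or on the cost-effectiveness plane. Report a ratio only with its quadrant named; when the non-antibiotic arm is cheaper with more UTIs, call it cost saved per additional UTI.

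The cost is a wording change and a little more analysis on data already to be collected. The one new decision is the range of values per UTI, because the protocol gives none.

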**10 Ethical considerations**

**10.1 Medical Ethics Committee**

Prior to implementation the protocol and the informed consent document and any subsequent modifications will be reviewed and approved by the ethics committee responsible for oversight of the study. The study coordinator is responsible for preparation of all documents and periodic reports required by the Medical Ethics Committee.

All investigators have to ensure that his trial will be conducted in accordance with the ethical principles that have their origin in the Declaration of Helsinki, and that are consistent with Good Clinical Practice.

- 1. **Informed consent**

The consent form will describe the purpose of the study, the procedures to be followed, and the risks and benefits, and the voluntary nature of participation. Prior to consent these items will be discussed and questions from subjects will be answered. Afterwards signed informed consent will be obtained by the study coordinator. A copy of the consent form will be given to the subject, and this fact will be documented in the subject’s record.

10.3 Subject confidentiality

All laboratory specimens, evaluation forms, reports, and other records that leave the site will be identified only by SID to maintain subject confidentiality. All records will be kept away from unauthorised persons. All computer entry and networking programs will be done using SIDs only. Clinical information will not be released without written permission of the subject, except as necessary for monitoring by the medical ethics committee.

10.4 Study modification/discontinuation

The study may be modified or discontinued at any time by the Medical Ethics Committee, or specific government agencies as part of their duties to ensure that research subjects are protected.

**10.5 Benefits and risks**

Participation in this study may help participants to reduce the number of symptomatic urinary tract infections they will experience. Study participants may experience discomfort associated with collecting material for urine, faecal or vaginal cultures.

Furthermore the trial will provide information on whether non-antibiotic prophylaxis can be considered as a serious alternative for antibiotic prophylaxis (that is care as usual) in pre- and post-menopausal women with recurrent UTIs.

11 Publication policy

The NAPRUTI-study is anticipated to result in several publications regarding the effectiveness, safety and cost-effectiveness of non-antibiotic prophylaxis compared to antibiotic prophylaxis (that is care as usual) in pre- and post-menopausal women with recurrent UTIs.

The Writing Committee of the main publication(s) will consist of the study coordinator and the principal investigators. Other members of the project group will be co-authors when they have made a significant contribution to the (subject of) the article. The order of co-authors will be determined by the amount of work which is provided by each of them.

All investigators not listed as co-authors will be acknowledged and will be individually listed in an appendix (as permitted by the scientific journal).

**Appendix I: List of definitions**

### Indication for prophylaxis: Patients with at least 3 or more symptomatic UTIs in the previous year before study inclusion.

### Postmenopausal women are all women, who have had their last menstruation at least one year before inclusion in the study.

### Premenopausal women are all women, who are not postmenopausal women.

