**3 Methodology**

- 1. **Study design**

The NAPRUTI study consists of two trials: RCT-A and RCT-B. Premenopausal women will be included in RCT-A, postmenopausal women in RCT-B. Both trials are multi-center, randomized double blind clinical trials with a follow-up time of 15 months.

Both trials consist of two parts: part one deals with UTI recurrence (non-inferiority part); part two aims to show a difference with respect to the development of bacterial drug resistance.

- 1. **Study duration**

Both trials will recruit 280 women. Patient enrolment is anticipated to last 2 years. After randomization patients will be followed for 12 months during which they will receive study medication and 3 months afterwards (“wash-out”-period). Total study duration will be 48 months.

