**4.2 Inclusion criteria and exclusion criteria**

**4.2.1 Inclusion criteria:**

- Women aged 18 years or older
- At least 3 symptomatic urinary tract infections, uncomplicated or complicated (for definitions see Appendix), in the year preceding study inclusion
  - 1. **Exclusion criteria:**

- Life expectancy </= 1 year

- Legally incapable

- A renal transplant in the medical history

- Contraindications for or

relevant interactions with co-trimoxazole (see Table 1)

RCT-A;

- Breastfeeding, pregnancy, or pregnancy wish for the next year

- Contraindications for or relevant interactions with cranberries (see Table 1)

Interactions of patient’s medication with study medication will be evaluated per patient. From each interaction the clinical relevance (risk for a particular patient) will be determined and the study coordinator will deliberate, along with the treating physician, in which way the interaction can be handled best.

Table 1, contra-indications and interactions with co-trimoxazole and cranberries.

| Study medication | Contra-indication | Interaction |
| --- | --- | --- |
| co-trimoxazole | allergy for sulfonamides and/or trimethoprim, severe renal or liver failure ( creatinin *or* ASAT and/or ALAT 5 times the upper limit) serious blood disorders, G6PD-deficiency, acute porphyria | oral anticoagulants, diuretics, sulfonylureumderi-vates, digoxin, methotrexate, fenytoin, procainamid, cyclosporine, folic acid antagonists, para-aminobenzoic acid and derivates |
| cranberries | known renal stones | oral anticoagulants |

If an eligible patient is using or has used cranberries, antibiotics, or estrogens (except oral contraceptives) in the 2 weeks in advance of screening, the patient is offered a “wash-out”-period before randomization.

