**5 Study Medication**

**5.1 Choice of drugs**

**5.1.1 Antibiotic prophylaxis**

It has been recommended to treat complicated UTIs with antimicrobials which achieve high tissue concentrations, such as trimethoprim-sulfamethoxazole (TMP-SMX or co-trimoxazole). Furthermore, TMP-SMX is also a good prophylactic for patients with a history of uncomplicated recurrent UTIs (8). Therefore, we want to administer TMP-SMX to the study participants.

- - 1. **Non-antibiotic prophylaxis**

In postmenopausal women lactobacilli are often absent. There is a strong positive relation between vaginal-colonization status and the risk of UTI. Therefore, we will use lactobacilli to prevent UTIs in postmenopausal women. We will use *Lactobacillus rhamnosus GR-1* and *L. reuteri RC-14.* Both possess properties that are required to colonize the vagina and inhibit uropathogens.

Premenopausal women will receive cranberry capsules as non-antibiotic prophylaxis. Because of problems with compliance and adherence to therapy with cranberry juice (18), we will use cranberry capsules for this study. Since premenopausal women have normal concentrations of vaginal lactobacilli, it makes no sense to give them additional lactobacilli capsules.

Detailed information about product characteristics and evidence of safety will be described in a separate supplement (Investigational Medicinal Product Documentation).

- 1. **Drug regimen, administration and duration**

RCT-A (premenopausal women). Women in the index group receive one cranberry capsules of 500 mg (in the morning and at bedtime) and one placebo tablet co-trimoxazole of 480 mg (ante noctum). Women in the reference group receive one tablet co-trimoxazole of 480 mg (ante noctum) and one placebo cranberry capsule (in the morning and ante noctum).

RCT-B (postmenopausal women): Women in the index group receive one capsule containing *Lactobacillus rhamnosus GR-1* and *L. reuteri RC-14 (>1*0e9 CFU) (in the morning and ante noctum) and one placebo tablet co-trimoxazole of 480 mg (ante noctum). Women in the reference group receive one tablet co-trimoxazole of 480 mg (ante noctum) and a placebo lactobacillus capsule (in the morning and ante noctum). Thus, in both trials each woman receives once a day one tablet and twice daily one capsule. All capsules and tablets must be taken by mouth for the duration of one year.

- 1. **Drug formulation, supply and distribution**

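### The one-year menstruation rule in Appendix I does not separate menopause from other amenorrhoea, and the breastfeeding and pregnancy exclusion is stated for RCT-A only

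*Protocol*

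**What the plan says.** Section 3.1 makes menopausal status the gate between the two trials: "Premenopausal women will be included in RCT-A, postmenopausal women in RCT-B".

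Appendix I defines that status by time since last menstruation: "Postmenopausal women are all women, who have had their last menstruation at least one year before inclusion in the study". The other group is its complement: "Premenopausal women are all women, who are not postmenopausal women". Neither definition mentions age, the cause of the amenorrhoea, hormone use, lactation or hysterectomy. The only age limit, in Section 4.2.1, applies to both trials: "Women aged 18 years or older".

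Section 4.2.2 gives exclusions common to both trials (life expectancy, legal incapacity, renal transplant, co-trimoxazole contraindications or interactions). It then lists, under RCT-A only, "Breastfeeding, pregnancy, or pregnancy wish for the next year". RCT-B has no list of its own.

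Section 5.1.2 justifies lactobacilli in RCT-B by their frequent absence after the menopause. It explains why they are not used in RCT-A: "Since premenopausal women have normal concentrations of vaginal lactobacilli, it makes no sense to give them additional lactobacilli capsules".

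**The concern.** The definition decides which product a woman can be randomised to, yet it does not identify the population that the rationale describes. A young woman who has not bled for a year for a reason other than menopause meets the rule for RCT-B. There she may be given the product that the protocol says has no purpose in premenopausal women.

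The exclusion list appears to rely on the same definition. Leaving breastfeeding and pregnancy out of RCT-B is harmless only if no woman in RCT-B can be breastfeeding or pregnant, and the one-year rule does not ensure that.

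At stake are whether RCT-B answers for postmenopausal women, as its objective states, and whether two halves of one protocol treat the same breastfeeding woman differently. Eligibility is settled before randomisation, so a later analysis plan cannot repair it.

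**Working it through.** No sample size, power or event figure enters this point, so there is no trial figure to reproduce. The check is to follow particular women through the text.

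**Step 1: which trial.** Sections 3.1 and 4.2.1 and Appendix I together give this rule: aged 18 or older and last menstruation at least one year ago, RCT-B; otherwise RCT-A.

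| Woman | Status under Appendix I | Trial | Fit with Section 5.1.2 |
| --- | --- | --- | --- |
| Aged 30, no bleeding for over a year on hormonal contraception | Postmenopausal | RCT-B | Conflicts |
| Aged 35, hysterectomy two years ago, ovaries in place | Postmenopausal | RCT-B | Conflicts |
| Breastfeeding, last menstruation over a year ago | Postmenopausal | RCT-B | Conflicts |
| Aged 75, hysterectomy years ago, ovaries in place | Postmenopausal | RCT-B | Fits |
| Pregnant, menstruated within the past year | Premenopausal | RCT-A, excluded there | Not applicable |

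Contraceptive users are foreseen: Section 4.2.2 exempts oral contraceptives from the wash-out offered for other estrogens.

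**Step 2: does another criterion catch the breastfeeding woman in RCT-B?** The common exclusions do not name her. The co-trimoxazole contraindications in Table 1 apply to both trials. They read "allergy for sulfonamides and/or trimethoprim, severe renal or liver failure" (with laboratory limits) and "serious blood disorders, G6PD-deficiency, acute porphyria", and name neither breastfeeding nor pregnancy. Section 7.1 excludes patients with contraindications but points back to the same list. Section 6.1 records pregnancy during follow-up, which is data collection and not an entry criterion.

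**Step 3: can a breastfeeding woman reach the one-year mark?** Assume 280 days from last menstruation to delivery. This figure is not in the protocol.

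- 365 − 280 = 85 days, about 12 weeks after delivery.
- With 259 days: 365 − 259 = 106 days, about 15 weeks.
- With 294 days: 365 − 294 = 71 days, about 10 weeks.

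So a woman still breastfeeding and without menses from about 10 to 15 weeks after delivery meets the postmenopausal definition.

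**Step 4: the pregnancy route.** A woman who menstruated in the year before inclusion is premenopausal and, if pregnant, is excluded in RCT-A. What remains is conception during a year or more of amenorrhoea, or a pregnancy wish or conception after entry to RCT-B.

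**The case against.** The best defence is that the authors plainly meant true menopause. The term defined is postmenopausal, the last menstruation is naturally read as the final one, and putting breastfeeding and pregnancy under RCT-A alone fits that intent. Section 4.1 has specialists determine eligibility and the study coordinator re-check it. Section 6.1 records age, history and medication at inclusion. A breastfeeding woman would have to pass both checks as postmenopausal, and would also need at least three symptomatic UTIs in the preceding year.

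This stands as a reason to expect few cases. It does not close the gap, because those checks apply the criteria as written, and as written she qualifies.

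Two stronger readings are tempting and should not be adopted.

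- A reader might infer that misclassified women dilute the lactobacillus effect in proportion to their number. The protocol gives no such number. RCT-B compares lactobacilli with co-trimoxazole, without a placebo-only arm, and these women would be randomised to both arms. The comparison stays unbiased for the women enrolled; the case mix shifts, and the direction of any change in the difference is unknown. Nor does the protocol state the vaginal flora of women with hormonal, lactational or post-hysterectomy amenorrhoea, or require absent lactobacilli for entry. Baseline vaginal lactobacilli are measured (Section 6.2, Table 2), so this could be examined.
- A reader might infer that RCT-B is generally open to pregnant women. Most pregnant women would be classed as premenopausal and excluded in RCT-A.

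**Conclusion.** The point holds as a conflict within the protocol. The Appendix I definition, applied as written through Section 3.1, sends some women with non-menopausal amenorrhoea to RCT-B, against the rationale in Section 5.1.2. It also makes an amenorrhoeic breastfeeding woman eligible for RCT-B although Section 4.2.2 bars her from RCT-A.

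The number of women concerned is not given and is probably small. No effect on power, the non-inferiority result or the estimate is claimed. The consequences are a less clearly defined RCT-B population and a gap in participant protection. The conclusion rests on the literal text. The only outside assumption is the 259 to 294 days used for the timing check, which affects when the breastfeeding case arises and not whether it can. Because the rule is stated and the remedy is short, it should be corrected and not left to judgement at screening.

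**What to change.** Reconcile Sections 3.1, 4.2.2 and 5.1.2 with Appendix I:

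1. In Appendix I, state that amenorrhoea with an evident non-menopausal cause does not by itself make a woman postmenopausal. Add a fallback based on age or menopausal status for women whose bleeding history is uninformative, such as after hysterectomy. The fallback is needed because Appendix I makes everyone else premenopausal: without it, simply ruling out hysterectomy with retained ovaries would move the 75-year-old in the table to RCT-A.
2. In Section 4.2.2, make the existing breastfeeding and pregnancy criterion consistent across both trials, so that it no longer depends on which side of the one-year line a woman falls. Its content is for the sponsor and the clinical investigators to settle.

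The cost is about two lines of protocol text and no new tests, since age, history and medication are already collected at inclusion. A few women would change trial or be excluded.
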